## Abstract

**Background:**

A Phase I study showed that it is feasible to implement a home-based self-management program aimed at increasing physical activity in individuals after stroke with mild walking disability in Brazil. The next step is to test this program against a control group in order to provide a power analysis for a fully-powered Phase III clinical trial.

**Methods:**

A Phase II pilot randomised clinical trial with concealed allocation, blinded measurement, and intention-to-treat analyses will be carried out. The inclusion criteria will be individuals diagnosed with stroke, in the acute or subacute phase, with mild walking disability, sedentary, and no significant language impairment. The participants will be randomly allocated to the experimental or control group. The experimental group will receive six sessions of a home-based self-management program based on behaviour change techniques through the Social-Cognitive Theory and Control Theory over 11 weeks. The control group will receive one session of education about stroke (regarding the importance of practising physical activity after a stroke) and usual care. A total of 24 participants will be recruited. The primary outcome will be physical activity, measured through steps taken per day by an activity monitor (Actigraph wGT3X-BT, Pensacola, FL, USA). The mean of daily steps will be analysed to compare groups after intervention. Secondary outcomes will be cardiovascular risk (body mass index, waist circumference, and blood pressure), depressive symptoms (Geriatric Depression Scale), walking ability (6-Minute Walk Test and 10-Meter Walk Test), exercise self-efficacy (Self-Efficacy for Exercise scale), social participation (Stroke Impact Scale) and quality of life (EuroQual-5D). Two-way analyses of variance will be implemented for all parametric outcomes, and the Kruskal–Wallis test for non-parametric outcomes will be used to determine the statistical significance of the between-group differences and reported as mean differences between groups (95% CI). All analyses will be conducted intention-to-treat. All outcomes will be measured at baseline (Week 0), post-intervention (Week 12), and follow-up (Week 24). This pilot clinical trial was registered online at Clinical Trials under number NCT05461976 on 4^th^ April 2022.

**Discussion:**

If beneficial, this Phase II pilot randomised trial will provide data to plan a fully powered future Phase III clinical trial aimed at verifying the efficacy of this program to promote physical activity after stroke.

**Trial registration:**

Clinical Trials NCT05461976 on 4^th^ April 2022.

**Supplementary Information:**

The online version contains supplementary material available at 10.1186/s12883-023-03461-7.

## Background

Keeping stroke survivors physically active is a challenge [1, 2]. Promoting physical activity after a brain lesion is essential to prevent recurrent events and associated risk factors [2]. However, stroke survivors face barriers in maintaining physical activity [1, 3]. *Behaviour change techniques* have been used after stroke to overcome these barriers [4]. Recently, a stroke guideline recommended that, in individuals with mild disability, implementing *behaviour change techniques* could have a positive impact on the level of physical activity [2].

One way to promote behaviour change after stroke is through self-management programs [4, 5]. These programs aim to help participants manage their condition by providing information and encouragement, which may be a good way of keeping stroke survivors physically active [5, 6]. There are cautious findings about the effectiveness of this strategy, suggesting the need for further studies in the area [4, 7, 8]. One review examined the evidence supporting self-management interventions for stroke survivors and reported some effectiveness in promoting physical activity [7]. Another review showed self-management programs based on *behaviour change techniques* were the most promising interventions to promote long-term free-living physical activity [4]. Finally, an integrative review describing the evidence around self-management interventions to improve mobility after stroke reported a deficient grade of evidence for the change in walking speed, endurance, balance, and physical activity (steps/day) [8].

Recently, we demonstrated the feasibility of implementing a home-based self-management exercise program to promote physical activity among stroke survivors with mild walking disability in Brazil [1]. Therefore, a Phase II trial is required to test this program against a control group to provide a power analysis for a fully-powered Phase III clinical trial. However, the feasibility analysis raised several essential points. First, the results revealed that sedentary participants, i.e., fewer than 5,000 steps per day, derived the most benefit from the program. Second, 59% of eligible individuals did not receive medical clearance to participate. Third, the primary barriers to physical activity were lack of support, knowledge, and accessibility. Fourth, only 28% of participants consistently filled in the diaries with information regarding their adherence to the program. Lastly, participants expressed that the measurement sessions were too long. A Phase II pilot randomised trial will address these issues and, in addition, we will answer the following questions:

(i)In sedentary individuals with a mild walking disability after stroke, does a home-based self-management exercise program promote physical activity (i.e., number of steps taken per day) more than usual care at 3 and 6 months?(ii)Does any improvement in physical activity carry over to improvements in cardiovascular risk, walking ability, depressive symptoms, exercise self-efficacy, social participation, and quality of life?

## Methods

### Design

A prospective, pragmatic, two-arm, parallel-group, Phase II pilot randomised clinical trial with concealed allocation, allocation ratio (1:1), blinded measurement, and intention-to-treat analyses will be carried out. The study was approved by the Federal University of Minas Gerais Ethics Board (65672517.6.0000.5149) Hospital Ethics Board (17/2017) and registered on clinicaltrials.gov on 4^th^ April 2022 (NCT05461976). Any modifications that may occur during this trial will be reported in clinicaltrials.gov.

### Recruitment

Individuals who have suffered a mild stroke after being discharged from a public hospital in Belo Horizonte City, Brazil and fulfilling inclusion criteria will be invited to participate by a research team member. The hospital is a stroke referral and accepts all kinds of patients (e.g. all ages, types of stroke, and severity).

### Inclusion criteria

The inclusion criteria will be the same as those for the feasibility study. The only exception now is that we will only include sedentary participants, as the feasibility study showed they benefited most from the program. Therefore, the inclusion criteria are: (1) time since stroke less than six months (2) ≥ 18 years of age; (3) able to walk ten meters independently at a speed ≥ 0.8 m/s without any walking devices; [9] (4) no cognitive impairments (determined by the cut-off scores on the Brazilian version of the Mini-Mental State Examination); [10] (5) sedentary (mean of steps counts < 5,000 steps/day [11], over four days, determined by a triaxial accelerometer—Actigraph wGT3X-BT, Pensacola, FL, USA). The exclusion criteria are (1) other neurological diseases; (2) comprehensive aphasia (evaluated by simple motor command); [12] (3) any other conditions that would prevent participation (e.g., recent post-surgery or surgery scheduled, travel or further compromise that prevents the participant from staying in Belo Horizonte during the intervention period).

### Procedures

Before starting the study, a research team member will provide complete study information for eligible participants. Those who fulfil the inclusion criteria, agree to participate and have received medical clearance will be invited to provide written consent. In order to overcome the lack of medical clearance found in the feasibility study, clinicians (not members of the research team) will be informed about the study’s objectives and the importance of physical activity for secondary prevention and encouraged to refer stroke survivors to the trial. During the study, who will be responsible for the participants will be the research team. After screening for eligibility and providing written consent, participants will be randomly allocated to either the experimental (home-based self-management program and usual care) or the control group (education and usual care).

### Data collection

Measurements will be collected in the hospital in Belo Horizonte City, Brazil, by trained researchers blinded to group allocation. Outcomes will be measured at baseline (Week 0), post-intervention (Week 12), and follow-up (Week 24) (see Fig. 1).

**Fig. 1 Fig1:**
[figure not shown]
Design of the trial

The measurement sessions will be restricted to 45 min. In the feasibility study, the duration of this section was 1.5 h, and participants expressed that it was too long (which may have influenced some participants’ decision to withdraw). To address this issue, we changed one instrument that measures social participation and reduced this section. We followed the SPIRIT checklist [13] to describe our protocol (see attached). The attached SPIRIT table (see Table 1) explains the schedule of this study and when enrolment, intervention/control group sessions and assessments will occur.

**Table 1 Tab1:** Schedule of enrolment, intervention, and assessment

	**Enrolment**	**Allocation**	**Weeks**								**Close-out**
**TIMEPOINT**	**-t2 (1 week before data collection in week 0)**	**-t1 (1 day before data collection in week 0)**	**0**	**1**	**2**	**3**	**5**	**7**	**11**	**12**	**24**
Eligibility screen	X										
Information consent	X										
Allocation		X									

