**ASSESSMENTS**											
Physical activity level			X							X	X
Cardiovascular risk			X							X	X
Walking ability			X							X	X
Depressive symptoms			X							X	X
Exercise self-efficacy			X							X	X
Social participation			X							X	X
Perception of quality of life			X							X	X

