### Randomisation

A computer-generated random allocation sequence will be used. Randomisation will be used to ensure balance (half in the experimental, half in the control). Index cards sequentially numbered according to the random assignment will be printed, folded, and placed in sealed opaque envelopes. A therapist, blinded to baseline measurements, will open the envelope, assign the participant to the corresponding study group, and book the first treatment session. Then, the therapist will deliver the intervention to the experimental group and the education session to the control group. Due to the characteristics of the intervention, it will not be possible to blind the therapist and participants to group allocation.

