### Primary outcome

A triaxial accelerometer will measure physical activity (Actigraph wGT3X-BT, Pensacola, FL, USA) [23]. Participants will be asked to wear the device on their waists and non-paretic sides [1]. They will be advised to wear the device during waking hours, except during water activities. The mean of steps taken per day over four days (two weekdays and two weekend days) will be recorded and reported in baseline (week 0), post-intervention (week 12) and follow-up (week 24) in both experimental and control groups. The mean of daily steps will be analysed to compare groups after intervention. As a way to describe the sample, the percentage of time spent in sedentary activities and moderate and vigorous physical activity will be reported at baseline, post-intervention, and follow-up in both groups. These data will not be used to compare groups after intervention. The Actigraph shows adequate psychometric properties in individuals after a stroke [23].

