### Sample size estimate

The present study is a Phase II pilot clinical trial and a specific intervention in a particular sample [sedentary individuals (> 5,000 steps/day) and with mild walking disability (gait speed ≥ 0.8 m/s] will be developed. So, data from the mean and standard deviation required to produce a sample size are unavailable in the literature. So, in this case, a formal sample size calculation will not be undertaken. To estimate the number of participants required in the present study, we will follow the recommendations of Julious et al., who support that 12 subjects per group are enough for pilot clinical trials [33, 34].

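### Table 1 places allocation one day before the Week 0 baseline measurements, which conflicts with the Randomisation section and may let participants record baseline after learning their group

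*Protocol article*

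**What the plan says.** Table 1 of the protocol article gives the order of events with explicit day counts. The eligibility screen and consent fall in the column "t2 (1 week before data collection in week 0", allocation in the column "t1 (1 day before data collection in week 0". In the assessment rows, "Physical activity level" and all other outcomes are marked at Weeks 0, 12 and 24 only.

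The text agrees with the table on when baseline is measured. The Data collection section puts it at Week 0, and the Primary outcome section says that the step mean "over four days (two weekdays and two weekend days) will be recorded and reported in baseline (week 0".

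The Randomisation section describes allocation thus: "A therapist, blinded to baseline measurements, will open the envelope, assign the participant to the corresponding study group, and book the first treatment session". It adds that neither therapist nor participants can be blinded. The Procedures section puts allocation after eligibility screening and written consent.

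On the sedentary criterion, the Inclusion criteria section has "sedentary (mean of steps counts < 5,000 steps/day [11], over four days", whereas the Sample size estimate section has "sedentary individuals (> 5,000 steps/day".

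**The concern.** A baseline should be fixed before anyone can know the allocation. Table 1 read literally reverses that order. A waist-worn step counter records what the participant chooses to do, and the self-efficacy, depression, participation and quality-of-life scales record what the participant chooses to answer. Blinded assessors protect neither. Someone who knows that a physical activity programme is about to start may walk more, or answer differently, in the days before it. Someone who knows that they will get a single education session may do the opposite.

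The Statistical analyses section makes baseline one of the three time points of the repeated-measures analysis of variance and allows baseline characteristics as covariates. A disturbed baseline would therefore enter the estimate that this pilot is meant to supply for Phase III planning.

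There is a second consequence. Missed sessions are to be filled with the most recent evaluation. A participant who leaves after allocation but before Week 0 has none, so the intention-to-treat plan has nothing to use for that person.

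**Working it through.** The point concerns order, so the plan has no figure to reproduce.

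**Calendar from Table 1.** Let day 0 be Week 0 data collection. Screening and consent are then on day -7 and allocation on day -1.

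- Wear starting at Week 0 covers days 0, 1, 2 and 3. All four are later than day -1, so 4 of 4 baseline days follow allocation.
- Four days of wear cannot fit in the single day between allocation and Week 0.
- Wear completed before the envelope is opened leaves 0 of 4 days after allocation.

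**Side by side with the text.** Shielding the allocating therapist from baseline results has a purpose if those results exist when the envelope is opened. Under Table 1 they do not. The two places can be squared only by a reading that neither states, for example that the therapist will also be kept from the results later.

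**Could a recording made between screening and allocation serve as baseline?** The baseline mean needs two weekdays and two weekend days, so the window must contain a whole Saturday and Sunday.

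- With full days -6 to -2 (five days), this works for 4 of the 7 possible start weekdays.
- With days -7 to -2 (six days), it works for 5 of 7.
- A window of seven consecutive days always works.

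The eligibility criterion asks only for four days, so this limit applies to a recording that doubles as baseline, not to screening itself.

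**How a disturbed baseline would enter the analysis.** Suppose that knowing the allocation shifts one arm's baseline mean by *d* steps/day and leaves later measurements unchanged.

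- Post-intervention difference alone: bias 0.
- Post-minus-baseline contrast between groups (part of the group-by-time term): bias -*d*.
- Analysis of covariance adjusting for that baseline with slope *b*: bias -*b* × *d*.

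The document gives neither *d* nor *b*. Purely as an assumed illustration, with *d* positive in the experimental arm:

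| Assumed *d* | Group-by-time contrast | Covariance, *b* = 0.5 | Covariance, *b* = 0.7 |
|---|---|---|---|
| 250 | -250 | -125 | -175 |
| 500 | -500 | -250 | -350 |
| 1,000 | -1,000 | -500 | -700 |

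The table shows how a shift carries through, not how large it would be. With *d* = 0 every entry is 0, and with *d* negative the signs reverse.

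**The case against.** The strongest reply is that the document conflicts with itself on the order and does not establish an unblinded baseline. The Randomisation wording fits a baseline measured first, and Fig. 1, which the Data collection section cites, is not available here and may settle the matter. Nothing says when participants learn their group. Booking a first session need not tell them, since both arms start with a home education session in Week 1 from the same therapist with the same described content. This stands, and it is why the point says that participants *may* know their group.

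It is also fair that a post-intervention comparison, which the abstract and the Primary outcome section describe, is untouched by a baseline shift, and that covariate adjustment is optional. But the Statistical analyses section specifies a repeated-measures analysis with baseline as a time point, so the exposure remains.

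A reader might go further and infer that people are randomised before it is known whether they are sedentary, because Table 1 shows no accelerometry before Week 0. The documents do not support that. The Procedures section and Table 1 both put eligibility screening before allocation, the step criterion is one of the inclusion criteria, and a four-day recording fits between the two columns. Gait speed and the cognitive test are also eligibility checks with no early mark of their own, so the single screening row plausibly covers all of them. What remains is that the article does not say whether the screening recording and the baseline recording are the same.

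Nor does the reversed sign in the sample size section bear on the sequence. The same phrase calls these people sedentary, and no formal calculation depends on it.

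**Conclusion.** The point holds as a contradiction about the order of allocation and baseline, with a possible bias if the schedule is followed as printed. Table 1 puts allocation on day -1 and all baseline measures at Week 0, while the Randomisation section implies the reverse. Under Table 1, with wear starting at Week 0, 4 of 4 baseline step days follow allocation.

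Bias in the group-by-time contrast, or in an analysis adjusted for that baseline, needs two further things that the document does not state: that participants learn their group before or during the baseline recording, and that this changes their walking or their answers. Neither its size nor its direction can be computed from the document. The gap for anyone who withdraws between allocation and Week 0 follows from the schedule and the carry-forward rule, but no number of such cases can be given.

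No conclusion is drawn that non-sedentary people would be randomised. The inequality sign is a separate clerical discrepancy.

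**What to change.** Change Table 1 and the Randomisation section to give one order: screening and written consent, then all Week 0 measures including the completed four-day accelerometry, then the envelope, then the first session in Week 1. If wear falls within days 0 to 6, the two-weekday, two-weekend pattern can always be met and the envelope can still be opened in time for Week 1.

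Add a sentence saying whether the screening step recording is also the baseline recording. If it is, the Week 0 mark for physical activity should be moved to match, and the window must be long enough for the weekday and weekend pattern. If it is not, say that the two recordings are separate.

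The cost is small: envelope opening moves later by a few days to a week, so the first session is booked at shorter notice. No extra visit or staff is needed. If practice already follows this order, only the wording changes. Participants who withdraw before the envelope is opened are then not randomised, and everyone randomised has completed the scheduled baseline.

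As a separate clerical correction, reconcile "sedentary individuals (> 5,000 steps/day" in the Sample size estimate section with "sedentary (mean of steps counts < 5,000 steps/day" in the Inclusion criteria section.

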**INTERVENTION**											
Home-based self-management				X	X	X	X	X	X		
Education about stroke, orientation and usual care				X	X	X	X	X	X		
**ASSESSMENTS**											
Physical activity level			X							X	X
Cardiovascular risk			X							X	X
Walking ability			X							X	X
Depressive symptoms			X							X	X
Exercise self-efficacy			X							X	X
Social participation			X							X	X
Perception of quality of life			X							X	X

### Randomisation

A computer-generated random allocation sequence will be used. Randomisation will be used to ensure balance (half in the experimental, half in the control). Index cards sequentially numbered according to the random assignment will be printed, folded, and placed in sealed opaque envelopes. A therapist, blinded to baseline measurements, will open the envelope, assign the participant to the corresponding study group, and book the first treatment session. Then, the therapist will deliver the intervention to the experimental group and the education session to the control group. Due to the characteristics of the intervention, it will not be possible to blind the therapist and participants to group allocation.

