	Review weekly schedule physical exercise;	Weekly activities calendar	Goal setting (behavior) (CT)
	Encouraging	Verbal therapist encouragement	Non-specific encouragement (SCogT)
	Review barriers and potential solutions	Paper-based barriers and solutions list	Problem-solving/coping planning (SCogT)
	Vicarious experience	Paper-based stroke survivors report about the self-management program (data from feasibility study)	Vicarious reinforcement (CT)
**Sessions 5 and 6**	Review goals	Goal Attainment Scaling	Review behavior goal(s) (CT)
	Review strategies to self-monitoring	Smartband and paper-based exercise diary	Self-monitoring of behavior (CT)
	Review weekly schedule physical exercise	Weekly activities calendar	Goal setting (behavior) (CT)
	Encouraging	Verbal therapist encouragement	Non-specific encouragement (SCogT)
	Review barriers and potential solutions	Paper-based barriers and solutions list	Problem-solving/coping planning (SCogT)

Legend: *CT* Control Theory, *ScogT* Social-Cognitive Theory

Session 1 will include education about stroke (what it is, symptoms, risk factors, how to prevent another event, and orientation regarding the importance of practising physical activity after a stroke).

In Session 2, the therapist will provide feedback about sedentary behaviour and the consequences of physical inactivity. Then, the participants will choose a target exercise through the Exercise Preference Questionnaire [18] and generate a list of goals using the Goal Attainment Scale (GAS) [19]. They will be asked to set short, medium and long-term goals using the GAS. In the first moment, participants will be encouraged to set short-term goals that are important to them and with low difficulty levels. As soon as short-term goals are achieved, they will be encouraged to attain medium-term goals (medium difficulty levels). Finally, long-term goals (high difficulty levels) will be added when the medium-term goals are achieved. At the end of the session, self-monitoring devices will be provided to participants. The focus is to show participants that they can perform a behaviour and to help them achieve it by increasing self-efficacy [14] and providing them with support and feedback [15].

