### Control group

The control group will receive one session of education about stroke (what it is, symptoms, risk factors, how to prevent another event, and orientation regarding the importance of practising physical activity after a stroke). This session will occur in the participant’s home, in person, on week 1, by the same therapist who will provide the intervention in the experimental group. In the subsequent weeks, they will receive usual care, which may include medical follow-up and guidance from other healthcare professionals (who are not involved with the research team) regarding the significance of behaviour change after stroke. It is a pragmatic study, so participants of both experimental and control groups will be allowed to perform daily living and healthcare activities (e.g., physiotherapy, occupational therapy, activities in a health centre, etc.).

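### Allocation is revealed before an education session that both arms share, an avoidable and probably modest risk of performance bias

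*Protocol article*

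**What the plan says.** The order of events is in the Randomisation section of the protocol article: "A therapist, blinded to baseline measurements, will open the envelope, assign the participant to the corresponding study group, and book the first treatment session". It continues: "Then, the therapist will deliver the intervention to the experimental group and the education session to the control group". The same section says that, because of the nature of the intervention, "it will not be possible to blind the therapist and participants to group allocation".

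Table 1 puts the allocation mark the day before the Week 0 measurements, and the first session of both arms in Week 1.

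The text under Table 2 describes the opening session of the program: "Session 1 will include education about stroke (what it is, symptoms, risk factors, how to prevent another event, and orientation", the orientation being about the value of physical activity. The Control group section gives the same list of topics for the control arm's one session. It adds that this session is given at home, in person, "on week 1, by the same therapist who will provide the intervention in the experimental group". After it, controls receive usual care.

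**The concern.** The two arms have a common first step. A session with the same stated content for everyone can be given by a therapist who does not yet know the allocation. The plan instead has it given by a therapist who knows which participants will not be visited again, and who is trained in the behaviour change techniques under test.

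Two departures are possible. The therapist may add goal setting, problem solving or encouragement for a control, which dilutes the contrast. Or the therapist may treat the control visit as a formality, which inflates it. Blinded assessors and an accelerometer outcome limit detection bias but do not protect against either departure.

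The Table 1 timing adds a second exposure. If participants learn their arm when the first session is booked, and booking follows allocation directly, they may know it while baseline steps, self-efficacy and depressive symptoms are being measured.

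What is at stake is the effect estimate that this pilot is meant to supply for planning the Phase III trial.

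**Working it through.** The point rests mainly on text, so the two sessions are set side by side.

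| Feature | Experimental Session 1 | Control session | Source |
|---|---|---|---|
| Topics | What stroke is, symptoms, risk factors, prevention, value of physical activity | Same list | Text under Table 2; Control group |
| Place | Home, in person | Home, in person | Intervention; Control group |
| Week | 1 | 1 | Table 1; Control group |
| Deliverer | The trial therapist | The same therapist | Randomisation; Control group |
| Behaviour change technique | None listed | None described | Table 2; Control group |
| Allocation known to therapist | Yes | Yes | Randomisation |

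**Where the arms diverge.** In Table 2 the technique column is empty for Session 1. The first entry, feedback on behaviour, is in Session 2. The table row for Session 1 omits the physical-activity orientation, but the text below it includes it, so the match with the control session holds.

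**Whether later disclosure fits the timetable.** Table 1 marks sessions in Weeks 1, 2, 3, 5, 7 and 11. The gaps are 1, 1, 2, 2 and 4 weeks, which agrees with the spacing described in the Intervention section. Session 2 comes one week after Session 1, which leaves time to open an envelope and book it.

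**The control row of Table 1.** It is marked at the same six weeks as the program, whereas the Control group section gives one session. The row combines education with usual care, which probably explains this. It is not used as evidence here.

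**How many are exposed.** 12 per group × 2 = 24, the stated total. All 12 controls have this as their only trial-delivered treatment session.

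**Size.** The article gives no SD, effect size or bias, so the following is illustration only, with every value assumed.

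- Precision of the pilot with 12 per arm: the 95% CI half-width is t(0.975, 22) × √(2/12) = 2.074 × 0.408 ≈ 0.85 SD.
- Phase III size per arm, two-sided 5% and 80% power: n = 2(1.960 + 0.842)²/d², with d in SD units, rounded up.

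| True effect | Bias | Effect seen | n per arm |
|---|---|---|---|
| 0.5 | none | 0.5 | 63 |
| 0.5 | −0.1 (controls coached) | 0.4 | 99 |
| 0.5 | +0.1 (control session thinner) | 0.6 | 44 |
| 0.5 | −0.2 | 0.3 | 175 |
| 0.5 | +0.2 | 0.7 | 33 |

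A bias of 0.1 SD is about 12% of the half-width (0.1/0.85), so it would be hidden within the sampling error of the pilot. Unlike that error, it is not reflected in the confidence interval.

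**The case against.** Much of the case on the other side is sound.

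- **The blinding statement.** A reader might infer that it is false. Read as a statement about the trial it is true: five of the six program sessions cannot be masked, and the fix would leave everyone unblinded from Session 2 on. It does not explain why allocation must be known at Session 1.
- **Only contact, and no reason.** A reader might say that controls have no other trial contact, or that the arrangement has no rationale. Controls also attend measurement visits at Weeks 0, 12 and 24, and the protocol does state a reason for not blinding. Using one therapist for both arms also avoids confounding arm with therapist, and the fix keeps this.
- **Unequal delivery is conjecture.** Correct. The plan sets the same topics for both sessions, and nothing in it shows that the therapist would depart from them. A script or fidelity check may be in the full protocol, so its absence from the article is no finding.
- **Magnitude.** A reader might suppose that coaching gives 3 of 12 controls the full program effect, shrinking the difference by 3/12 = 25%. One education visit cannot plausibly match six sessions over 11 weeks with goal setting, self-monitoring devices and a supervised exercise session. The documents do not support that figure.
- **The trial is pragmatic and compares the program with usual care.** This stands, but controls already receive the education session, so delaying disclosure does not change the planned contrast.
- **Allocation concealment.** A therapist who has met the participant would then open the envelope. This is a real cost. It is met if the envelope number is fixed to the participant beforehand and the envelope is opened after the visit, so that neither the choice of envelope nor added coaching during that visit can depend on the arm.

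**Conclusion.** The point holds as an avoidable weakness in sequence. Allocation is disclosed before a session with the same stated content, setting, week and therapist in both arms and, by the Table 1 schedule, before the baseline measurements. Neither is needed, because the arms diverge only at Session 2.

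The consequence is a possible performance bias of either sign, and possible influence on baseline measures. Its size is unknown and probably modest. For a pilot, priority is low to moderate. The main reason to act is that the remedy is cheap and the effect estimate is intended for Phase III planning.

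The conclusion assumes that the two topic lists describe the same session and that Table 1 gives the intended timing. If the Table 1 timing is a slip and allocation in fact follows the Week 0 measures, the baseline part falls away and the part about the shared session remains.

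**What to change.** Change the sequence as follows.

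1. At consent, assign the next sequentially numbered sealed envelope to the participant and log the number.
2. Complete the Week 0 measures.
3. Give every participant the same Session 1, with the same booklet.
4. Open the envelope only after that visit, when Session 2 would be booked.

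Amend the Randomisation section to say that the therapist and participants are unaware of allocation until after Session 1 and unblinded thereafter. Move the allocation mark in Table 1 to between Weeks 1 and 2.

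The cost is protocol wording and one column of a table, with no added visit, staff or content. There are two downsides:

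- People who withdraw before or during Session 1 are no longer randomised. They should be counted and reported as pre-randomisation losses, so that this information is kept for Phase III planning. A few more people may need to be consented to reach 24 randomised, and the protocol should say what happens to their unopened envelopes.
- The therapist will have met the participant before opening the envelope, which is why the number must be fixed at consent.
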